# An observational cohort study of interstitial lung abnormalities (ILAs) in a large Japanese health screening population (Kumamoto ILA study in Japan: KILA-J)

**DOI:** 10.1186/s12890-023-02455-y

**Published:** 2023-06-08

**Keywords:** Interstitial lung abnormality (ILA), Idiopathic pulmonary fibrosis, Progressive pulmonary fibrosis (PPF)

## Abstract

**Background:**

Interstitial lung abnormalities (ILAs) are subtle or mild parenchymal abnormalities observed in more than 5% of the lungs on computed tomography (CT) scans in patients in whom interstitial lung disease was not previously clinically suspected and is considered. ILA is considered to be partly undeveloped stages of idiopathic pulmonary fibrosis (IPF) or progressive pulmonary fibrosis (PPF). This study aims to clarify the frequency of subsequent IPF or PPF diagnosis, the natural course from the preclinical status of the diseases, and the course after commencing treatment.

**Methods:**

This is an ongoing, prospective, multicentre observational cohort study of patients with ILA referred from general health screening facilities with more than 70,000 annual attendances. Up to 500 participants will be enrolled annually over 3 years, with 5-year assessments every six months. Treatment intervention including anti-fibrotic agents will be introduced in disease progression cases. The primary outcome is the frequency of subsequent IPF or PPF diagnoses. Additionally, secondary and further endpoints are associated with the efficacy of early therapeutic interventions in cases involving disease progression, including quantitative assessment by artificial intelligence.

**Discussion:**

This is the first prospective, multicentre, observational study to clarify (i) the aetiological data of patients with ILA from the largest general health check-up population, (ii) the natural course of IPF or PPF from the asymptomatic stage, and (iii) the effects and outcomes of early therapeutic intervention including anti-fibrotic agents for progressive cases of ILA. The results of this study could significantly impact the clinical practice and treatment strategy for progressive fibrosing interstitial lung diseases.

**Trial registration number:**

UMIN000045149.

**Supplementary Information:**

The online version contains supplementary material available at 10.1186/s12890-023-02455-y.

## Background

An interstitial lung abnormality (ILA) is defined as “incidental identification of non-dependent abnormalities on computed tomography, including ground-glass or reticular abnormalities, lung distortion, traction bronchiectasis/bronchiolectasis, honeycombing, and non-emphysematous cysts involving at least 5% of a lung zone in individuals in whom interstitial lung disease is not suspected [1–3]. The clinical importance of ILAs has been increasingly recognised as early and asymptomatic lesions in cases of progressive fibrosing interstitial lung diseases (ILDs) [4, 5]. Furthermore, the presence of ILAs is a prognostic factor in ILD, lung cancer, and chronic obstructive pulmonary disease (COPD). This is because ILAs are subcategorised as non-fibrotic and fibrotic, with fibrotic abnormalities thought to represent early or mild pulmonary fibrosis, resulting in a higher risk of complications in lung cancer or COPD [1–3, 6]. Although an asymptomatic period in which ILAs can be detected during high-resolution computed tomography (HRCT) examinations is likely to precede a pulmonary fibrosis diagnosis, the natural history of progression from ILA stage to overt disease remains unknown [4, 5]. This challenge has remained unresolved with progressive pulmonary fibrosis (PPF) as a newly defined pathological concept characterised by progressive fibrosis as well as IPF [5, 7]. Furthermore, the effect of early anti-fibrotic drug therapies for ILA on progressed disease stages is unknown. However, anti-fibrotic drugs have effectively prevented the decline of forced vital capacity (FVC) with a potential for improved IPF or PPF prognoses [8, 9].

The frequency of ILA and predictors of ILA progression have been identified in large studies on COPD cases and populations at risk of cardiovascular diseases [3, 6]. In addition to age, smoking history, body mass index (BMI), and genotype being predictive background factors for ILA progression [3, 6, 10], HRCT findings and patterns of ILA have also been identified as progression and prognostic factors [10–12]. However, there is limited data on ILA in many general check-up populations [12]. Hence, this study aims to clarify the natural course from ILA or the asymptomatic stage in patients subsequently diagnosed with IPF or PPF and the course and outcome after the introduction of therapeutic interventions. Additionally, this study also aims to clarify the frequency and progression index of ILA by analysing ILA cases screened from general health screening facilities with the largest number of examinees.

## Methods/design

### Study design

This is a prospective, multicentre observational cohort study on ILAs diagnosed by respiratory specialists from general health screening facilities in Kumamoto Prefecture, Japan. Other details of the study’s design are as follows:

Presence or absence of invasion: Mild invasion (no new needle insertion with plasma blood sampling at enrolment:)Presence or absence of intervention: No intervention.Presence or absence of use of samples collected from the human body: Yes (plasma and serum are stored).Positioning of the study: observational study.Randomisation: None.

### Participant characteristics

#### Study population

Eligible candidates are not only cases with suspected ILA on chest CT at health check-up facilities, but also cases confirmed by the health check-up facilities to have reticular shadows at the costophrenic angles on chest X-ray with or without the presence of fine crackles on auscultation, assuming no history of interstitial pneumonia. Training sessions will be held for physicians in the screening check-up facilities participating in the study to confirm the study participants using any of these three findings. Cases with either of these findings in the screening check-up facilities are suspected cases of ILA. The study will enrol approximately 500 patients from > 70,000 examinees in general health check-up facilities, annually screened by chest radiography, with fine crackles on auscultation and/or CT findings. Participants will be enrolled over 3 years and followed up for 5 years. The primary outcome is the evaluation of the aetiological data of preclinical patients who are subsequently diagnosed with IPF or PPF. This study has been designed according to the Strengthening the Reporting of Observational Studies in Epidemiology Statement guidelines. Patients or the public were involved in the design, conduct, reporting, or dissemination plans of our research.

#### Inclusion criteria

Patients with one or more of the following findings during check-ups will be suspected of having ILAs which are slightly modified in the Fleischner Society criteria [1]: (i) fine reticular shadows at the costophrenic angles on chest radiography, (ii) fine crackles on auscultation, and (iii) lower predominant subpleural reticular shadows on CT findings. Patients suspected to have ILAs at a screening facility will be referred for further examination in any of the three teaching hospitals (Kumamoto University Hospital, Japanese Red Cross Kumamoto Hospital, and Saiseikai Kumamoto Hospital) where pulmonologists work. Patients diagnosed with ILAs confirmed using HRCT who provided informed consent will be enrolled into the study’s database.

This study defines ILAs as subtle or mild parenchymal abnormalities observed in > 5% of the lungs during CT examination of patients in whom ILD has not been previously clinically suspected.

The final diagnosis for ILA based on the diagnosis using HRCT by the pulmonologists in each case will be confirmed in institutional conferences of the three teaching hospitals. This can be strengthened by having a concordant diagnosis by a radiologist who is an expert in respiratory diseases or by concordance with more than two pulmonologists who reviewed the records of each patient who met the inclusion criteria.

#### Exclusion criteria

The following are exclusion criteria: (i) patients who refuse to participate in the study after reading the explanation, (ii) patients with acute or subacute progressive interstitial pneumonia, (iii) patients who have difficulties undergoing the periodic follow-up due to their distant places of residence, (iv) cases that are assessed as inappropriate for the study by medical attendants, (v) cases incorporated into intervention studies, such as clinical trials that are not allowed to participate in observational studies.

### Data collection and management

#### Primary endpoint

The primary endpoint is the frequency of subsequent IPF or PPF diagnoses.

#### Secondary endpoints

The secondary endpoints are (i) frequency of ILA cases among all general health examiners and (ii) frequency of fibrotic hypersensitivity pneumonitis and collagen vascular diseases related to interstitial pneumonia in patients diagnosed with PPF.

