### Statistical analysis

#### Sample size calculation

There are ≥ 70,000 examinees yearly for the Japanese Red Cross Kumamoto Hospital Health Care Center and the Center for Preventive Medicine of Saiseikai Kumamoto Hospital. The number of participants suspected of having ILAs was approximately 300 at each centre in 2018. Therefore, the total number of participants with ILAs is assumed to be approximately 600 per year.

According to the previous data, the number of cases will be underestimated by 10% because approximately 10% of the medical check-ups that require detailed tests for ILAs did not undergo the subsequent detailed examinations. Therefore, the maximum number of suspected ILAs is expected to be 500 cases annually.

Continuous variables will be expressed as means and standard deviation (SD), or medians and interquartile ranges (IQRs), and categorical variables for each group will be expressed as the number of subjects and percentages. The inter-observer variation in the presence or absence of HRCT findings will be analysed using the weighted kappa statistic and classified as follows: poor (κ = 0–0.20), fair (κ = 0.21–0.40), moderate (κ = 0.41–0.60), substantial (κ = 0.61–0.80), and almost perfect (κ = 0.81–1.00). Inter-observer variation regarding the extent of the HRCT findings was assessed using Spearman’s rank correlation coefficient. The HRCT scores assigned by the two independent observers are compared using the Bland–Altman method. If the HRCT patterns or scores do not agree between the two radiologists; one of the patterns or scores is adopted by consensus.

All analyses with ILA progression as the outcome variable are performed using logistic regression, where ILA progression was dichotomised with progression defined as probable or definite progression, and regression defined as no change, probable regression, and definite regression using subjective visual estimation as well as an objective AIQCT. Multivariable analyses will be adjusted for variables such as age, sex, and smoking status. In addition, a Cox proportional-hazards model has been created to assess treatment efficacy, considering the immortal period as a time-dependent covariate.

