### Aetiological data of patients with ILA from the general health check-up population

The AGES-Reykjavik study, an epidemiological study including patients aged ≥ 40 years at risk of cardiovascular lesions, reported that 378 (7%) patients with ILAs on initial HRCT were observed from 5320 participants. Furthermore, 327 of 378 patients who underwent subsequent CT scans were evaluated for ILA progression [6, 10]. The AGES-Reykjavik study reported that 238 (73%) of 327 participants eventually showed ILA progression over 5 years (median: 5.1 years). ILA progression was also assessed in 1867 participants in the Framingham Heart Study using serial CT scans [6, 11]. The study reported that 155 (8%) of 1867 participants showed ILAs on initial CT scans. Furthermore, 119 (76%) of the 155 participants showed ILA progression on serial CT scans during the 6-year follow-up period. In a CT lung cancer screening program, 41 (2.4%) of 1699 subjects had ILA on baseline CT and 10 (24.4%) of 41 patients with ILA were subsequently diagnosed ILD after more than 4 years [16].

Although these studies did not describe the specific diagnoses in cases that showed ILA progression, the mortality rate from pulmonary fibrosis in the group with ILA was reported to be as high as 47% in the AGES-Reykjavik study.

The prevalence of ILA in an Asian health screening cohort of 2765 patients was reported to be approximately 3% [13]. The present clinical study is supposed to include a large number of participants with ILAs observed on HRCT, especially in the largest population (> 210,000 examinees) of general health check-ups. Hence, the study’s primary and further endpoints will be achieved.

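### Secondary endpoint (i) divides ILA found by selective screening by all examinees, so it measures screen-detected yield and is likely to understate ILA frequency

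*Protocol article*

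**What the plan says.** Secondary endpoints in the protocol article lists "i) frequency of ILA cases among all general health examiners". The denominator is therefore fixed as all examinees.

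The route to becoming a case is narrower. Study population describes the examinees as "annually screened by chest radiography, with fine crackles on auscultation and/or CT findings". Under Inclusion criteria, any one of three findings (radiograph, auscultation, CT) raises suspicion, suspects are referred to one of three teaching hospitals, and ILA is confirmed there on HRCT. The article does not say that every examinee has a CT and does not give the share who do. Sample size calculation and Study limitations both report that about 10% miss the follow-up examination.

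On size, the abstract speaks of "general health screening facilities with more than 70,000 annual attendances", and Sample size calculation says "There are ≥ 70,000 examinees yearly". The Discussion subsection on aetiological data refers to ILA being observed "especially in the largest population (> 210,000 examinees) of general health check-ups". The same subsection says "The prevalence of ILA in an Asian health screening cohort of 2765 patients was reported to be approximately 3" per cent, and gives 2.4% on baseline CT in a lung cancer screening programme.

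**The concern.** ILA is defined on CT, so a frequency over all examinees needs either CT in everyone or an allowance for those not imaged. Here an examinee who has ILA but a clear radiograph, no audible crackles and no check-up CT stays in the denominator and cannot enter the numerator. Later analysis cannot recover a case that was never imaged.

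The Background names clarifying the frequency of ILA as a study aim, and the Discussion mentions this screening population next to published prevalences. A reader would naturally take the result as the prevalence of ILA in a general health-check population and conclude that ILA is rarer than it is. Study limitations mentions missed re-evaluation but neither undetected ILA nor repeat attendance.

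The 210,000 raises a second, separate question: whether people or visits are being counted.

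**Working it through.** **Inputs from the protocol article**

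- Examinees per year: at least 70,000 (abstract; Sample size calculation).
- Suspected ILA: about 300 at each of two centres in 2018, so about 600 a year; expected maximum 500 a year (Sample size calculation).
- Enrolment: "Up to 500 participants will be enrolled annually over 3 years", so at most 3 × 500 = 1,500.
- Comparison figures: 3% and 2.4% (Discussion).

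**Step 1: the plan's total.** 3 × 70,000 = 210,000. This reproduces the Discussion figure exactly, so it is a sum of annual attendances.

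**Step 2: expected frequency = cases / examinees.**

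| Cases per year | / 70,000 | 3% divided by this | 2.4% divided by this |
|---|---|---|---|
| 600 | 0.86% | 3.5 | 2.8 |
| 540 (600 less 10%) | 0.77% | 3.9 | 3.1 |
| 500 | 0.71% | 4.2 | 3.4 |

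The expected yield is thus 2.8 to 4.2 times below the two quoted figures, or roughly 3- to 4-fold.

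**Step 3: can non-attendance explain the gap?** 10% of 600 is 60 people, and 60 / 70,000 = 0.09 percentage points. The loss that the protocol discloses is small beside the distance to 2.4% or 3%.

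**Step 4: suspected versus confirmed.** The 500 to 600 are suspected cases before HRCT. The confirmation rate is not given. If 75% were confirmed (assumption), the frequency would be 0.54% to 0.64%, or 4.7 to 5.6 times below 3%. If 50% were confirmed (assumption), it would be 0.36% to 0.43%, or 7.0 to 8.4 times below.

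**Step 5: repeat attendance.** Let r be the share of attenders in years 2 and 3 who were already seen in an earlier year (not given, so the full range is shown). Unique people = 70,000 × [1 + 2(1 − r)].

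| r (assumed) | Unique people | 210,000 / unique | 1,500 / unique | 3% divided by this |
|---|---|---|---|---|
| 0 | 210,000 | 1.0 | 0.71% | 4.2 |
| 0.5 | 140,000 | 1.5 | 1.07% | 2.8 |
| 0.75 | 105,000 | 2.0 | 1.43% | 2.1 |
| 1 | 70,000 | 3.0 | 2.14% | 1.4 |

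The first row is the same 0.71% as in step 2. If 1,500 cases are found and each is counted once, moving to unique people narrows the gap. Repeat attendance is then part of the 4.2 and does not multiply it.

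**The case against.** The endpoint is a descriptive secondary one and is worded as a frequency, not a prevalence. The Background ties it to cases screened at health facilities, the 10% non-attendance is disclosed, and the reason for referral is already recorded (Data collection). An article may also leave the counting of persons to the full protocol. All of this is fair, and it limits the point to what the endpoint can be said to measure. It does not remove the mismatch, because the article itself fixes both the denominator and the selective route to HRCT.

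Several stronger readings are tempting but unsupported:

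- **That most cases come from radiograph or crackles.** No breakdown by route is given, and CT is itself one of the three triggers.
- **That 210,000 is the endpoint's denominator.** It appears only in the Discussion, as a statement of study size.
- **That repeat attendance multiplies the 3- to 4-fold gap.** Step 5 shows otherwise for the planned 1,500. It would add to the gap only if three-year cases fell well short of that number, which the article does not say.
- **That the cohorts with 7% and 8% show an even larger shortfall.** One was selected for cardiovascular risk at age 40 or over and the other was a heart-study cohort, so population differences cannot be separated from detection.
- **That the yield divided by 3% is the share of ILA captured.** The yield counts suspected cases, so this is not a capture rate.
- **That a comparison with published prevalences is planned.** None is stated. The article also does not say how ILA was ascertained in the 3% cohort.
- **That refusers are left out of the numerator.** The endpoint refers to ILA cases, not enrolled participants, so this is open.

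**Conclusion.** The point holds in a limited form. As written, secondary endpoint (i) gives the yield of a selective screening pathway over all examinees and is likely to understate ILA frequency. Measured against the protocol's own quoted 2.4% and 3%, the expected 0.71% to 0.86% is about 3- to 4-fold lower. That size assumes those cohorts are a reasonable guide to this population, which differences in age and risk may undermine, and it treats every suspected case as confirmed. It is not established that the result will be too low by any particular factor, because neither the CT share nor the number of unique people is given.

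The 210,000 is a sum of attendances described as a population of examinees. If it were used as the denominator with each case counted once, that denominator would be inflated between 1.0- and 3.0-fold, depending on the return rate. This is a separate issue and should not be stacked on the 3- to 4-fold gap. The primary endpoint is unaffected.

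**What to change.** 1. Name endpoint (i) *screen-detected ILA yield*, with unique examinees as denominator and each person counted once over the three years. State that examinees who were not flagged had no confirmatory HRCT.
2. Split it by the recorded reason for referral. Say whether refusers count as cases, and give a range for non-attenders and refusals, from none to all of them having ILA.
3. Add *ILA prevalence among unique examinees who had a check-up chest CT*, with those people as denominator. Note that they are self-selected. Note also that the CT trigger in Inclusion criteria (subpleural reticular change, mainly in the lower lung) is narrower than the ILA definition, which in the Background includes ground-glass change and cysts, so some ILA may be missed even here.
4. Make any comparison with CT-based prevalences only with the figure in item 3.
5. In the Discussion, describe the 210,000 as attendances.

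The cost is two counts from the facilities' records (unique examinees, and unique examinees with a check-up CT) and rewording. The reason for referral is already collected at enrolment; for people not enrolled it would have to come from the referral record. Nothing changes for participants. The drawback is that the CT denominator is smaller and less representative of all examinees.

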#### Further endpoints

The progression rate of ILA cases will be examined using HRCT. In addition, IPF cases involving patients with ILA will be evaluated for (i) the rates of decline in FVC, percentage diffusing capacity for carbon monoxide (%DLco), and 6-min walk distance; and (ii) the progression rate of the ILD-Gender–Age–Physiology (ILD-GAP) GAP Index. Rate of decline in 6-min walk distance in cases of IPF diagnosed from ILA patients.

The progression rate of HRCT findings in IPF cases involving patients with ILA will be assessed by comparing the visual and quantitative assessments using artificial intelligence-based quantitative CT (AIQCT) [13]. In addition, the progression rate of HRCT findings in PPF cases involving patients with ILA will be assessed by comparing the visual and quantitative assessments using AIQCT. Furthermore, the proportion of HRCT findings showing progression in IPF or PPF cases before and after therapeutic interventions will be assessed by comparing the visual and quantitative assessments using AIQCT.

Other endpoints to be assessed include: (i) the association between HRCT progression indices and functional indices or clinical outcomes in patients with IPF or PPF, (ii) the rate of FVC decline before and after anti-fibrotic drug therapy in IPF and PPF cases involving patients with ILA, (iii) mortality rates of IPF from the asymptomatic stage, (iv) incidence of acute exacerbation in IPF and PPF cases from the asymptomatic stage, (v) the frequency of respiratory complications (pneumonia, lung cancer, and others) requiring inpatient treatment of patients with IPF or PPF from the asymptomatic stage, (vi) rate of decline in %DLco before and after therapeutic intervention in PPF cases involving patients with ILA, and (vii) the output score of image AI to assess suspicions of interstitial pneumonia from chest X-rays [14].

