Patients that show any signs of disease progression, including the appearance of clinical symptoms, decline in lung function, or exacerbation of HRCT findings evaluated by visual assessment and AIQCT [13], will be considered for a full work-up and the introduction of drug therapy. The detailed examination will include bronchoalveolar lavage (BAL), transbronchial lung cryobiopsy, or surgical lung biopsy. After registration, subsequent pulmonary complications requiring hospitalisation, such as acute exacerbation, pneumonia, pneumothorax, or lung cancer, will be recorded.

Furthermore, it will be recorded if long-term oxygen therapy is needed in cases of progression despite appropriate medication during the follow-up years. When therapeutic intervention is introduced, the assessment plan is reset, and regular assessments are carried out during the period from the introduction of treatment (Supplementary Table 2).

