#### Timing of the start of treatment

Regular mandatory check-ups are carried out every six months by a registered researcher at a medical screening centre and progression is assessed according to the Progressive Fibrosing-Interstitial Lung Disease progression criteria [15]. If deemed to be a progression, the facility MDD will also be consulted and a decision will be made to introduce therapeutic agents.

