### Specific MDD for cases progressing from the ILA stage and response to early therapeutic intervention

It has been reported that 20% of ILA cases progress within 2 years, and > 40% progress within 5 years [1, 2]. As well as increasing age, smoking history, BMI, and increasing copies of *MUC5B* promoter polymorphism being predictive background factors for ILA progression [3, 6, 11], the fibrotic signs of lung distortion, traction bronchiolectasis/bronchiectasis, and honeycombing on HRCT imaging are considered to be crucial for the progression of ILA and poor prognosis [10, 12, 17, 18]. However, there has been little data about how many patients are subsequently diagnosed with IPF or PPF. Furthermore, the natural history of the asymptomatic phases corresponding to the ILA stages in these progressive fibrosing phenotypes has not been elucidated. A recent meta-analysis showed that anti-fibrotic treatment reduces the risk of all-cause mortality in progressive fibrosing phenotypes, including IPF [8, 9]. However, it is critical to determine whether the early identification and diagnosis of these fibrotic ILDs could lead to early treatment, resulting in a better prognosis [5]. The present study’s flow is to assess the ILA stage every 6 months. Once clinical progression is confirmed, a full examination will be considered, including BAL and biopsy, according to the 2022 International Guidelines, and the degree of confidence in the MDD. Clarification on the progression from ILA to an advanced disease stage and treatment responsiveness in the respective pathologies of IPF and PPF is expected.

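### The before/after contrasts for FVC, %DLco and HRCT are taken around a treatment start prompted by observed progression, so they should not be read as drug effect

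*Protocol article*

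**What the plan says.** Three contrasts under Further endpoints compare treated patients with themselves across the start of therapy:

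- FVC: "the rate of FVC decline before and after anti-fibrotic drug therapy in IPF and PPF cases involving patients with ILA".
- %DLco: "rate of decline in %DLco before and after therapeutic intervention in PPF cases involving patients with ILA".
- HRCT: "the proportion of HRCT findings showing progression in IPF or PPF cases before and after therapeutic interventions will be assessed". The sentence goes on to say that visual reading and AI-based quantification will be compared for this.

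The start of therapy depends on observed worsening. Data collection says: "Patients that show any signs of disease progression, including the appearance of clinical symptoms, decline in lung function, or exacerbation of HRCT findings" "will be considered for a full work-up and the introduction of drug therapy". Timing of the start of treatment says that, at six-monthly check-ups, "progression is assessed according to the Progressive Fibrosing-Interstitial Lung Disease progression criteria", and then: "If deemed to be a progression, the facility MDD will also be consulted and a decision will be made to introduce therapeutic agents".

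The Abstract (Methods) ties the secondary and further endpoints to how well early treatment works. Neither secondary endpoint concerns treatment, so the further endpoints carry that claim. The Abstract (Discussion) and the main Discussion say the study will clarify the effects of early therapy in progressive cases. Study design states that there is no randomisation. The statistical section adds a Cox model for treatment efficacy with a time-dependent covariate for the immortal period.

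**The concern.** An observed FVC is the true value plus measurement error. A visit that reaches a progression threshold tends to carry a low error, so part of the fall is chance. That visit triggers therapy and closes the pre-start series, which is then too steep on average. The next value tends to be higher whether or not a drug is given. If the triggering value also opens the post-start series, that slope is too shallow as well. The same reasoning applies to %DLco. For HRCT the selection is more direct: a start made because HRCT worsened has progression beforehand by construction.

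At stake is a stated aim of the study. Read as evidence on early therapy, these contrasts can show improvement with an inert drug. The Cox model does not help, because it handles immortal time in a time-to-event analysis and does not touch a within-patient change in slope.

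**Working it through.** The article gives no figure to reproduce here. It states no FVC variance and no size of decline for the trigger, so every size below rests on assumptions. Only the six-monthly visits and the 5-year follow-up come from the document. The drug effect is set to zero throughout. False benefit means post-start slope minus pre-start slope, so a positive value favours the drug.

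**1. FVC in % predicted, trigger on a 12-month fall.** Assumed: mean true slope -1, -2 or -3 points/yr (between-patient SD 1, 1.5, 2), error SD 0, 1.5, 2.5 or 4 points, trigger 5 or 10 points.

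Example with mean slope -2, error SD 2.5, trigger 5. The true slope of those triggered is -2.30.

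- Twelve months up to the trigger against the next twelve: -7.11 and +0.03. False benefit = 0.03 - (-7.11) = 7.14 points/yr. Of this, 7.11 - 2.30 = 4.81 is the pre-start slope being too steep and 0.03 + 2.30 = 2.33 is the post-start slope being too shallow.
- Slope over all visits up to the trigger against a slope from later visits only: -3.76 and -2.29. False benefit = 1.47 points/yr, nearly all from the pre-start side.

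Over all settings with error SD 1.5 to 4, the first comparison gave about 3.9 to 16.8 points/yr and the second about 0.8 to 2.7. With error SD 0, before equalled after in every setting where anyone triggered. This identifies the artefact as regression to the mean.

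**2. FVC in mL, trigger on decline from enrolment.** Assumed: true slope -80 mL/yr (SD 40), baseline 3,000 mL, at least two values before the trigger, per-person slopes. Bias of the pre-start slope in mL/yr:

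| Trigger | Triggering value | Noise SD 80 | 100 | 150 |
|---|---|---|---|---|
| 10% | included | -29 | -46 | -87 |
| 5% | included | -38 | -49 | -75 |
| 10% | excluded | -2 | -4 | +1 |
| 5% | excluded | +26 | +40 | +80 |

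Excluding the triggering value nearly removes the bias at 10% but over-corrects at 5%, which would hide a real benefit.

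False benefit with the post-start slope opened one visit later: 35 to 73 mL/yr in one run and 35 to 100 in another, that is 35/80 = 44% to 100/80 = 125% of the assumed mean decline. With the triggering value in both slopes, runs gave 57 to 159.

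The bias shrinks with longer run-ins. With at least three prior values the pre-start slope was too steep by 1 to 49 mL/yr. When slopes were pooled with more weight on long series, its bias was -17 to +5. If only half of starts are prompted by FVC, the per-person figures roughly halve.

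**3. Decline that accelerates.** Background and Discussion both say the natural history is unknown, so linear decline is itself an assumption. Assumed instead: base slope -30 mL/yr, 40% of participants worsening by an extra 100 to 200 mL/yr from a random time, noise SD 80 to 120, trigger 5 to 10%. The contrast ran from -31 to +87 mL/yr, favouring the inert drug in 6 of 8 settings. A second run with assumed acceleration gave -53 to +52.

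**4. Linear mixed model on all enrolled participants, slope change at therapy start.** With linear truth its bias was -2 to 0 mL/yr. With accelerating truth it was -97 to +2 in one run and about -116 to -6 in another, which mostly hides benefit.

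**5. HRCT.** If a share *f* of starts is prompted by HRCT worsening, scored by the same reading method, the pre-start proportion with progression is at least *f*. Within those starts it is 100%, so the post-start proportion can only equal it or be lower, whatever the drug does.

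**The case against.** The strongest reply is that the article fixes no estimator. It names quantities and does not say whether the triggering value belongs to the pre-start slope, the post-start slope or both. Slope modelling is commonly left to the SAP or full protocol, and the figures above depend heavily on it. This stands against any single size. It does not remove the point: the contrast itself, taken around a start chosen because of decline, is in the endpoint definitions.

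Second, Data collection says the assessment plan is reset when treatment begins, with a supplementary table that is not shown. That may mean a fresh post-start baseline, which would remove the post-start part of the bias. The pre-start part would remain.

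Third, the facility MDD is consulted, and the FVC and %DLco endpoints cover diagnosed IPF or PPF cases only, so some chance triggers would be screened out. This reduces the size. However, PPF is characterised in Background by progressive fibrosis, so restricting to it again selects on decline.

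Fourth, the HRCT sentence can be read as comparing two reading methods. That is fair, but its quantity is still progression before against after therapy.

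A reader might also infer that the sections contradict each other on when to treat, since Data collection speaks of any sign and Timing of the start of treatment of formal criteria plus MDD. The text reads naturally as two steps: a sign leads to consideration, and the criteria with MDD lead to a decision. The Discussion's "Once clinical progression is confirmed, a full examination will be considered, including BAL and biopsy" concerns the work-up and fits that reading. Nor do the documents show that the three hospitals start therapy at different points; they share data and hold regular joint case conferences.

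**Conclusion.** The point holds for the FVC, %DLco (PPF cases) and HRCT before/after contrasts. Where the start was prompted by the measure being compared, regression to the mean makes the pre-start decline look too steep and can make an inert drug look helpful. HRCT-prompted starts carry pre-start progression by selection. The effect is weaker where a different sign prompted the start.

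The size cannot be taken from the documents. Under linear decline and the assumed noise it is large against the assumed decline. Under acceleration even the net direction can reverse. Two stronger readings should be resisted. One is that the bias always favours the drug, which needs linear decline. The other is that a linear mixed model cures it, which needs the same assumption. A reader might also suppose that the primary endpoint is compromised; it counts IPF or PPF diagnoses and does not use these contrasts, so the effect there is limited.

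These are further endpoints in a declared observational study, so the study as a whole is not undermined. The change is still worth making, because it alters what may be concluded about early treatment.

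**What to change.** 1. Record in the EDC the date and type of the sign that led to each treatment start (FVC, %DLco, HRCT, symptoms).
2. Report the before/after FVC, %DLco and HRCT contrasts by trigger type (same measure against other) as descriptive results, and state that no efficacy claim is drawn from the raw contrast.
3. Open the post-start series at the first assessment after the start, not at the triggering value.
4. Add two sensitivity analyses: (a) pre-start slopes without the triggering value; (b) a mixed model on the six-monthly values of all enrolled participants, treated or not, with a slope change at therapy start and allowance for non-linear decline. State that (a) over-corrects when the trigger is small, and that (b) hides benefit if decline accelerates and linearity is assumed.

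Cost: a few EDC fields and some extra analysis, with no change to care. Pre-start slopes without the triggering value are less precise (SD about 15 to 41% larger in the simulation), and patients triggered at the first six-month visit, up to about 32% of triggers in the simulated settings, lose that slope altogether. The result remains non-causal.
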